## Abstract

**Introduction:**

The impact of stroke-related impairment on activities of daily living may vary between patients, and can only be estimated by applying patient-reported outcome measures. The International Consortium for Health Outcome Measurement has developed a standard set of instruments that combine clinical and longitudinal patient-reported outcome measures for stroke. The present study was designed (1) to implement and evaluate the feasibility of the use of it as a consistent outcome measure in clinical routine at the stroke center of a German university hospital, (2) to characterize impairment in everyday life caused by stroke, and (3) to identify predictive factors associated with patient-relevant outcomes.

**Methods:**

We plan to enroll 1040 consecutive patients with the diagnosis of acute ischemic stroke, transient ischemic attack, or intracerebral hemorrhage in a prospective observational study. Demographics, cardiovascular risk factors, and living situation are assessed at inpatient surveillance. At 90 days and 12 months after inclusion, follow-up assessments take place including the Patient-reported Outcomes Measurement Information System 10-Question Short Form (PROMIS-10), the Patient- Health Questionnaire-4, and the simplified modified Ranking Scale questionnaire. The acceptance and feasibility (1) will be assessed by a process evaluation through qualitative semi-structured interviews with clinical staff and patients and quantitative analyses of the data quality evaluating practicability, acceptance, adoption, and fidelity to protocol. The primary outcome of objective 2 and 3 is health-related quality of life measured with the PROMIS-10. Additional outcomes are depressive and anxiety symptoms and patient participation in their social roles. Patient-reported outcomes will be assessed in their longitudinal course using (generalized) mixed regressions. Exploratory descriptive and inference statistical analyses will be used to find patterns of patient characteristics and predictive factors of the outcome domains.

**Perspective:**

The results will describe and further establish the evaluation of stroke patients of a stroke center by standardized PROMs in everyday life.

**Trial registration:**

The trial is registered at ClinicalTrials.gov (NCT03795948). Approval of the local ethics committee (Ethik-Kommission der Ärztekammer Hamburg) has been obtained.

## Introduction

Stroke is a major cause of death and disability worldwide. Although the mortality of stroke has decreased through improved treatment by new interventions and more efficient management strategies, the overall societal burden of stroke has further grown during the last decades [8, 17]. Three months after stroke, about 40% of stroke patients are either dead, living in a nursing home, or depending on continuous care from others [12]. Direct deficits resulting from stroke, e.g. paresis or aphasia, are easily spotted, and well characterized by clinical rating scales, which are used in clinical practice. There are, however, indirect consequences of stroke which are more difficult to detect unless they are looked for by purpose. Stroke patients are known to suffer from problems with impaired cognition, anxiety, and depression amongst others, which in turn, affect functional status, and satisfaction in daily living, and which often only become manifest in the long term in everyday life as outpatients [1, 16, 23]. These highly relevant consequences of stroke are often missed in standard assessments by physicians or in clinical scales applied by stroke researchers.

The past years have brought a movement towards a more patient-centered evaluation of quality and value in health care, summarized by the term of `value-based healthcare´ [20, 21]. In this context, the evaluation of quality of care and treatment success by patient-reported outcome measures (PROMs) play a central role [10, 24]. Retrospective studies of patients after mild ischemic, and hemorrhagic strokes have reported altered quality of life using PROMs of the National Institute of Health’s Patient-reported Outcome Measurement Information System (PROMIS), showing changes in physical, social, and mental domains [15]. To overcome the problem of the great variability of PROMs used for assessment, the International Consortium for Health Outcomes Measurements (ICHOM) has coordinated the development of a consensus Standard Set of PROMs for Stroke based on PROMIS in order to enable comparable assessment of healthcare value in stroke management across different settings [13, 14, 22]. There is, however, a lack of data on patient-reported outcomes of stroke management from routine clinical practice. Studies reporting process evaluation of implementation of PROMs in the clinical practice are also scarce, although in form of process evaluations, facilitators and barriers of such an implementation can be discovered, and the implementation process can be adjusted for a successful realization of the desired intervention or enquiry.

## Methods

### Aim of the trial

The objectives of the current study are to implement the ICHOM-Standard Set for Stroke (ICHOM-SSS) in routine stroke care, and appraise this implementation, i.e. the acceptance and feasibility of its use in clinical practice by means of a process evaluation, to systematically characterize the long-term functional status and health-related quality of life after stroke in a longitudinal setting, and to identify factors influencing outcome and course of outcome after stroke. The addressed research questions are to which extend can the ICHOM-SSS be implemented into the routine health care for stroke patients and how are acceptance, benefit, and feasibility appraised by patients and clinical staff? How is the outcome of stroke and stroke treatment in a consecutive sample and which medical and patient-related factors influence the treatment outcome?

### Study description and study design

We perform a prospective exploratory observational and implementation study with a longitudinal design. The sample consists of a consecutive cohort of patients referred to the stroke unit at the University Medical Centre Hamburg-Eppendorf for acute ischemic or hemorrhagic stroke within a 15 months period.

### Inclusion/exclusion criteria

Inclusion criteria are:treatment at the stroke unit of our hospital with acute ischemic stroke (AIS) [ICD10 I63], transient ischemic attack (TIA) [ICD10 G45], or intracerebral hemorrhage (ICH) [ICD10 I61]informed consent by the patient or legal guardian

Exclusion criteria are:severe disturbances of the ability to communicate, i.e. due to severe aphasia, dementia;insufficient knowledge of the German or English language.

### Sample size estimation

In the past years, approximately 1300 patients with a relevant diagnosis were admitted at the stroke unit of our hospital annually. Of these patients, 60% had an ischemic stroke, 32% had a transient ischemic attack, and 8% were admitted with intracerebral hemorrhage. With an expected dropout of approximately 25%, we aim to include *n* = 1040 patients (Fig. 1). This number allows for exploratory descriptive and inferential analyses with high precision and power, including subgroup analyses and the use of multivariate and longitudinal models. While the planned analyses are of exploratory nature, sample size calculations, done with GPower [7] show that in order to identify a small effect (H0 ρ^2^ = 0.01 and H1 ρ^2^ = 0.05 in a two-sided test with a power of 0.90, a regression analysis with 25 predictors the analysis of data of 846 cases are necessary, which is below the expected sample size.

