Research questions 2 and 3: The data will be analysed by descriptive and inferential statistics, Depending on the outcome, (generalised) multilevel linear (patient-reported global health) and logistic (mental and motor health) regression analyses will be conducted. Factors that are believed to possibly influence the outcomes will be integrated in form of covariates. These will comprise demographics, pre-existing deficits and prior strokes, and deficits at admission (NIHSS) since recent studies have shown a negative influence of impaired motor function on different PROMIS domains(Katzan, Thompson, et al., 2018). Additionally, survival analyses (mortality) will be performed. Exploratory structural equation models are fitted to identify differential characteristic patterns of the outcomes. Further, exploratory subgroup analyses are planned, using regression models that fit the respective research questions. Results with *p* < .05 will be considered as statistically significant. As this study is of explorative nature, no adjustments for multiple testing will be made. However, the elevated risk of an occurrence of type-I errors will be regarded at the interpretation of the results. Missing values will be accounted for by using mixed modelling techniques. Sensitivity analyses will be performed when no mixed models are used. The influence of the NIHSS on the outcomes will be analysed separately using median and nonparametric tests.

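### The sample size section claims high power for subgroup analyses, but its only calculation is for the whole cohort, and no diagnosis group is large enough to carry that calculation

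*Protocol article*

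**What the plan says.** The section Sample size estimation says of the planned 1040 patients: "This number allows for exploratory descriptive and inferential analyses with high precision and power, including subgroup analyses". The calculation given in support uses "H0 ρ^2^ = 0.01 and H1 ρ^2^ = 0.05 in a two-sided test with a power of 0.90" and concludes that for "a regression analysis with 25 predictors the analysis of data of 846 cases are necessary". It concerns a single model in the whole cohort. No power or precision figure is given for any subgroup.

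The same section gives the case mix of past admissions: "60% had an ischemic stroke, 32% had a transient ischemic attack, and 8% were admitted with intracerebral hemorrhage". It also gives an expected dropout of about 25%.

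In Data analysis and management, "exploratory subgroup analyses are planned, using regression models that fit the respective research questions". Neither the subgroups nor the number of predictors per subgroup model is fixed. The significance threshold is p "< .05 will be considered as statistically significant", without adjustment for multiple testing. The Perspective section expects the analysis to help find groups of patients at raised risk of poor quality of life.

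**The concern.** High power for subgroup analyses is asserted as a property of the design, next to figures that allow a check. If 846 cases are needed for the stated test, a diagnosis group of 624 or fewer cannot have the stated power for it.

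A reader who trusts the sentence would treat a null result in TIA or hemorrhage as informative. In hemorrhage the opposite risk also arises. A model with many predictors in some 60 to 80 patients explains a large share of variance by chance, so apparent patterns of predictors would be hard to tell from noise.

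**Working it through.** **Inputs.** From Sample size estimation: null 0.01 and alternative 0.05 for the squared multiple correlation ρ², 25 predictors, two-sided test, power 0.90, 846 cases, case mix 60/32/8%, dropout 25%, n = 1040. The α of 0.05 comes from Data analysis and management, since the sample size section gives none. As in the plan's own calculation, each patient contributes one observation.

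**Method.** Exact distribution of the sample R² with random predictors: R² given J is Beta(p/2 + J, (N − p − 1)/2), with J negative binomial with size (N − 1)/2 and success probability 1 − ρ². Critical values are the 2.5% and 97.5% points under ρ² = 0.01. Power is the probability of falling outside them under ρ² = 0.05.

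**The plan's own figure.** One-sided at α = 0.05 this gives N = 846 (power 0.9001), so the method matches the one used. The two-sided test that the text states needs 980 and has power 0.84 at 846. That is a separate matter; the subgroup result below does not depend on it.

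**Group sizes.** It is unclear whether the 25% is still to come off 1040, so both readings are carried.

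- Dropout after enrolment: 1040 × 0.75 = 780. Then 780 × 0.60 = 468, 780 × 0.32 = 249.6 (250), 780 × 0.08 = 62.4 (62).
- All 1040 analysed: 1040 × 0.60 = 624, 1040 × 0.32 = 332.8 (333), 1040 × 0.08 = 83.2 (83).

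**Power for ρ² = 0.05 against 0.01** (ranges run from 780 to 1040 analysed)

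| Setting | Ischemic stroke | TIA | Hemorrhage |
|---|---|---|---|
| 25 predictors, two-sided | 0.49–0.67 | 0.22–0.32 | 0.06–0.07 |
| 25 predictors, one-sided | 0.61–0.77 | 0.32–0.43 | 0.08–0.10 |
| 10 predictors, two-sided | 0.65–0.80 | 0.34–0.47 | 0.08–0.10 |
| 5 predictors, two-sided | 0.72–0.85 | 0.42–0.55 | 0.11–0.14 |

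For comparison, the whole cohort (25 predictors, two-sided) has 0.80 at 780 and 0.92 at 1040. With 468/250/62 analysed, the smallest ρ² detectable with 90% power is 0.085, 0.141 and 0.478.

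**Tests of single factors.** The article gives no effect size for one factor, so partial R² is an assumption. I used an F test with 1 and N − 26 degrees of freedom, λ = N × R²/(1 − R²), 24 other covariates, α = 0.05 two-sided, and 468/250/62 patients. At partial R² = 0.05, λ is 24.6, 13.2 and 3.26.

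| Partial R² | Ischemic stroke | TIA | Hemorrhage |
|---|---|---|---|
| 0.05 | 0.999 | 0.95 | 0.42 |
| 0.04 | 0.99 | 0.90 | 0.35 |
| 0.02 | 0.87 | 0.61 | 0.19 |

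With 83 hemorrhage patients and partial R² = 0.05, λ = 83 × 0.05/0.95 = 4.37 and power is 0.54, still low.

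**Precision of a mean T-score.** The 95% half-width is 1.96 × 10/√N. The SD of 10 is the reference-population value in Outcome measures and is assumed to hold for these patients. At 468/250/62 it is 0.9, 1.2 and 2.5 points.

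**Overfitting in hemorrhage.** Patients per predictor: 62/25 = 2.5 to 83/25 = 3.3. Expected R² with no association at all is p/(N − 1): 25/61 = 0.41, or 25/82 = 0.30.

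**The case against.** The strongest reply is that the figures test a model the plan does not propose. The 25 predictors belong to the whole-cohort calculation, the subgroup models are left to fit their question, and no subgroup is named. This stands, so the figures are conditional. Diagnosis is nevertheless the only split the section quantifies, and cutting the model to 5 predictors leaves every group below 0.90. Ischemic stroke passes 0.90 only under changed terms with all 1040 analysed: about 0.91 for a one-sided test with 5 predictors, or 0.94 for a one-sided test against zero with 25. TIA and hemorrhage stay at or below 0.67 and 0.21 in those settings.

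Second, 1040 may already be net of dropout: 1300/1.25 = 1040, and the text calls 846 lower than the expected sample, which cannot be true of 780. The abstract, however, speaks of enrolling 1040. Both readings are open, hence the ranges.

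Third, the search for predictive factors rests on single coefficients, not on an overall R² test. This also stands. A reader might infer that subgroup models would mostly miss real effects. The single-factor figures do not support that for ischemic stroke, and in TIA it depends on effect size. It is a fair description of hemorrhage only.

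Fourth, the analyses are declared exploratory, and the plan promises caution about type I error. That justifies doing subgroup analyses; it does not support calling them highly powered.

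**Conclusion.** The statement of high power for subgroup analyses is not supported by the protocol's own inputs. With diagnosis as the subgroup and the stated effect, no group reaches 0.90 in a two-sided test with 5, 10 or 25 predictors. TIA does not exceed 0.55 and hemorrhage does not exceed 0.14. The exact values rest on three assumptions: subgroups by diagnosis, the same overall test in each, and 780 to 1040 patients analysed.

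Two stronger readings are not supported. A reader might infer that the precision claim fails as well, but half-widths of about 0.9 and 1.2 T-score points are good for ischemic stroke and TIA; only hemorrhage, at about 2.5, is clearly poorer. A reader might also infer that the plan will take significance in one diagnosis and its absence in another as a difference between them. Nothing in the article proposes this, and groups at raised risk can be identified in the pooled model. The fault is an overstated claim, not the planning of exploratory subgroup work.

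**What to change.** - Limit the high-power statement to the whole cohort, and say whether 1040 is before or after dropout.
- State the expected analysed size of each diagnosis group (Fig. 1, not visible in the text reviewed, may already show numbers by diagnosis), with the power and precision ranges above and their assumptions.
- Test differences between diagnoses as diagnosis-by-factor interactions in the pooled model, for a short list of factors named in advance.
- Do not fit a 25-predictor model in hemorrhage; report that group descriptively with confidence intervals.

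No extra patients or data are needed. The cost is a less favourable claim and fewer separate subgroup models. Interaction tests will also have limited power; their merit is that they address a difference between diagnoses directly.

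### The 846 cases in the power statement fit a one-sided test; the two-sided test named in the same sentence needs 980 at the 0.05 level, and its power at 846 is about 0.84, not 0.90.

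*Protocol article*

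**What the plan says.** The Sample size estimation section of the protocol article contains the plan's only formal power calculation. Its hypotheses are "H0 ρ^2^ = 0.01 and H1 ρ^2^ = 0.05". The test and the resulting number are given as "a two-sided test with a power of 0.90, a regression analysis with 25 predictors the analysis of data of 846 cases are necessary", and GPower is named as the software. The section concludes: "the analysis of data of 846 cases are necessary, which is below the expected sample size".

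No significance level appears in that section. The one level in the article is in Data analysis and management: "Results with *p* < .05 will be considered as statistically significant". Neither a one-sided test nor a 0.10 level is mentioned anywhere.

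**The concern.** The sentence gives every input except alpha, so once alpha is taken from the analysis section the required number can be recomputed. At the two-sided 0.05 level the stated inputs do not lead to 846. The match with the one-sided 0.05 answer, to the exact integer, suggests that a one-tailed calculation was reported as two-sided.

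At stake is the credibility of the statement offered to show that the cohort is large enough. A reader comparing the analysable sample with 846 would be using a benchmark 134 cases too low for the test described. If the number analysed fell between 846 and 979, that reader would wrongly conclude that 0.90 power had been reached.

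**Working it through.** **Inputs**

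- Null ρ₀² = 0.01, alternative ρ₁² = 0.05, p = 25 predictors, power 0.90, two-sided: Sample size estimation.
- Alpha = 0.05: Data analysis and management. This is the one assumption, because the sample size section states no alpha.

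**Method**

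A non-zero null for ρ² calls for the exact distribution of the sample R² with random (multivariate normal) predictors. It is a mixture:

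- K follows a negative binomial distribution with size (N − 1)/2 and success probability 1 − ρ².
- Given K = k, R² follows Beta(p/2 + k, (N − p − 1)/2).

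Write F(x; N, ρ²) for the resulting distribution function.

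- One-sided: find c with F(c; N, 0.01) = 0.95. Power = 1 − F(c; N, 0.05).
- Two-sided: find c_L and c_U with F(c_L; N, 0.01) = 0.025 and F(c_U; N, 0.01) = 0.975. Power = 1 − F(c_U; N, 0.05) + F(c_L; N, 0.05).

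**Step 1: reproduce 846**

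One-sided at 0.05 with N = 846, the critical value is c = 0.0579 and power is 0.9001. At N = 845 power is 0.8996. The smallest N is therefore exactly 846.

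**Step 2: the test the plan names**

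Two-sided at 0.05 with N = 846, the critical values are c_L = 0.0213 and c_U = 0.0621. The upper region gives power 0.8371; the lower region adds about 0.000002. Power is 0.837.

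Solving for 0.90: N = 979 gives 0.89997 and N = 980 gives 0.9004. The smallest N is 980.

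| N | One-sided 0.05 | Two-sided 0.05 |
|---|---|---|
| 780 | 0.870 | 0.796 |
| 845 | 0.8996 | 0.8366 |
| 846 | 0.9001 | 0.8371 |
| 975 | 0.942 | 0.898 |
| 980 | 0.943 | 0.9004 |
| 1040 | 0.956 | 0.921 |

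**Step 3: size of the discrepancy**

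- Cases: 980 − 846 = 134, and 134/980 = 13.7%.
- Type II error at 846: 1 − 0.837 = 0.163, against the 0.10 claimed.

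**Step 4: could another setting explain 846?**

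- Simulation with 400,000 draws: at N = 846, power 0.901 one-sided and 0.838 two-sided; at N = 980, 0.901 two-sided. This agrees with the exact results.
- Predictors: 24, 25 and 26 give two-sided N of 969, 980 and 990.
- Two-sided alpha with 25 predictors: 0.01 gives 1270, 0.025 gives 1107 and 0.10 gives 846. The 0.10 match is expected, since its upper critical value is the one-sided 0.05 value.
- Fixed predictors (noncentral F, null 0.01): 839 with an upper tail of 0.05 and 971 with 0.025, so the gap does not depend on the random-predictor model.
- Null ρ² = 0: 559 to 635, nowhere near 846.

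Of the two-sided settings tried, only alpha = 0.10 returns 846.

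**The case against.** Four points can be made for the plan.

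1. **Alpha is inferred.** The analysis section sets a threshold for reporting results, not necessarily the input to the power software, and 846 is right for a two-sided 0.10 test. This stands as a caveat. But the article never uses 0.10, and a power statement at a level the study does not apply would also need correcting.
2. **The word may be wrong, not the number.** The alternative lies above the null, the aim is to detect an effect, and the lower rejection region contributes practically nothing to power. On that reading 846 answers the natural upper-tailed question and only the label is mistaken. This is fair, and the article does not settle it. The two repairs deserve equal standing, and the 134-case shortfall applies only if a two-sided 0.05 test was intended.
3. **The conclusion can survive.** Against 1040, 980 is still smaller and two-sided power is 0.92; the margin shrinks from 1040 − 846 = 194 to 1040 − 980 = 60. If the 25% dropout is instead taken from 1040, 0.75 × 1040 = 780 remain. That is already below 846, so sidedness is not what causes that shortfall. Sidedness alone changes the comparison only for an analysed number from 846 to 979.
4. **The calculation did not set the target.** The 1040 is presented alongside annual admissions and expected dropout, and the study is declared exploratory. This limits the consequences and is why no added recruitment follows. It does not reconcile the stated number with the stated test.

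**Conclusion.** The concern holds. At alpha 0.05 the two-sided description and the figure of 846 cannot both be right: 846 is the exact one-sided answer, the two-sided answer is 980, and two-sided power at 846 is 0.837. The result rests on alpha = 0.05 from the analysis section and on the random-predictor model; the fixed-predictor model shows nearly the same gap. That the software was run one-tailed is a strong inference from the exact match, not something the article shows. The practical effect is limited, because 980 remains below 1040 and nothing confirmatory depends on the figure. It is nonetheless an error in the plan's only formal power statement and should be corrected.

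**What to change.** Correct the power sentence in Sample size estimation and state alpha there. Any one of these makes it consistent:

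- keep the two-sided test at alpha 0.05 and replace 846 with 980;
- keep 846 and describe the test as one-sided at alpha 0.05;
- keep 846 and the two-sided test at alpha 0.05, and report the power as 0.84.

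The authors should choose according to the test they intended. Then restate the comparison with the expected sample using the corrected figure, saying whether 1040 is counted before or after the 25% dropout: two-sided power is 0.92 with 1040 analysed and 0.80 with 780.

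The cost is a short rewording and a less favourable statement if the two-sided test is kept. No change to recruitment or analysis is required by this point.
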